## Abstract

**Background::**

The administration of Janus kinase inhibitors as well as biological disease-modifying anti-rheumatic drugs has dramatically improved the clinical outcomes of patients with rheumatoid arthritis (RA). Previous trials have shown that upadacitinib, a Janus kinase inhibitor, can effectively improve disease activity and prevent progression of joint destruction in RA patients with inadequate responses to methotrexate (MTX). It remains unclear whether reduced disease activity can be maintained after discontinuation of MTX in patients treated with upadacitinib plus MTX. Thus, the aim of this study is to evaluate changes in disease activity after administration of upadacitinib plus MTX in RA patients who failed to achieve an adequate response to MTX and to determine whether clinical relapse can be avoided after discontinuation of MTX in those who achieved clinical remission.

**Methods/design::**

The proposed study is an interventional, multicenter, open-label, single-arm clinical trial with a 48-week follow-up. The cohort will include 155 RA patients with at least moderate disease activity during treatment with MTX. Patients will receive upadacitinib and MTX will be discontinued for those who achieve clinical remission. Disease activity will be evaluated longitudinally by measuring clinical disease activity indices and with musculoskeletal ultrasound (MSUS). The primary endpoint is the proportion of patients who sustain a disease activity score-28- C reactive protein score of ≤3.2 from week 24 to 48 after a disease activity score-28- C reactive protein score of <2.6 at week 24. Important secondary endpoints are changes from baseline MSUS scores. Serum levels of multiple biomarkers, including cytokines and chemokines, will be comprehensively analyzed.

**Discussion::**

The study results are expected to show the clinical benefit of the discontinuation of MTX after achieving clinical remission by treatment with upadacitinib plus MTX combination therapy. The strength of this study is the prospective evaluation of therapeutic efficacy using clinical disease activity indices and standardized MSUS, which can accurately and objectively evaluate disease activity at the joint level among patients drawn from multiple centers. Furthermore, parameters to predict clinical remission after administration of upadacitinib plus MTX combination therapy and nonclinical relapse after discontinuation of MTX will be screened by integrated multilateral assessments (i.e., clinical disease activity indices, MSUS findings, and serum biomarkers).

## Introduction

1

Rheumatoid arthritis (RA) is a chronic autoimmune disease that causes synovitis in multiple joints.^[1]^ Because uncontrolled RA can lead to joint destruction and functional disability, management of RA based on the “treat-to-target” strategy is important to control disease Activity.^[2]^ Methotrexate (MTX) is a first-choice conventional synthetic disease-modifying anti-rheumatic drug (csDMARD) for treatment of active RA. However, a considerable proportion of RA cases are refractory to MTX. In addition, adverse events (AEs) and tolerability issues may occur with long-term use of MTX. Thus, the next treatment choice is important for RA patients refractory to or intolerant of MTX. Janus kinase (JAK) inhibitors in addition to biological DMARDs (bDMARDs) have been used in the second phase of the European League Against Rheumatism (EULAR) recommendations, lading to better clinical outcomes, such as the achievement of clinical remission for patients with RA.^[3]^

Upadacitinib is a selective JAK1 inhibitor developed by AbbVie (Chicago, IL). The addition of JAK inhibitors, including upadacitinib, was reported to achieve clinical remission in nearly half of RA patients with inadequate responses to MTX.^[4,5]^ Although there is little evidence, as the next step, it is important to determine whether minimal disease activity can be maintained even if MTX is discontinued after achieving clinical remission in patients treated with a combination of JAK inhibitors and MTX. Thus, it is necessary to investigate the maintenance of clinical non-relapse after discontinuation of MTX in RA patients who achieved clinical remission with upadacitinib plus MTX combination therapy.

Musculoskeletal ultrasound (MSUS) is widely applied as an imaging modality for clinical assessment of RA patients.^[6,7]^ MSUS provides more accurate detection of synovial inflammation as compared to a clinical examination. In addition, MSUS is noninvasive, objective, relatively inexpensive, repeatable, and thus well-suited for treatment monitoring.^[6,7]^ It is therefore important to assess disease activity and therapeutic response using MSUS as well as the clinical disease activity indices, including subjective parameters.^[6–9]^ However, very few prospective multicenter collaborative studies have used standardized MSUS to evaluate the disease activity of RA.

We will evaluate the changes in disease activity by using MSUS as well as clinical disease activity indices so that the patients’ disease activity will be assessed with greater accuracy. In addition, MSUS will be used to determine whether nonclinical relapse can be maintained after discontinuation of MTX by RA patients who achieved clinical remission. Furthermore, serum biomarker levels will also comprehensively analyzed. Lastly, patient parameters will be screened to predict nonclinical relapse after discontinuation of MTX by integrating multilateral assessments, including the clinical disease activity indices, MSUS findings, and serum biomarkers.

This clinical trial was named the “Discontinuation of methotrexate in rheumatoid arthritis patients achieving clinical remission by treatment with upadacitinib plus methotrexate (DOPPLER)” study. Herein, the final protocol (version 1.5; July 27, 2021) of the DOPPLER study is described.

## Objectives

2

### Primary objective

2.1

The principal objective of the study is to determine the proportion of RA patients who maintained nonclinical relapse after discontinuation of MTX after achieving clinical remission with upadacitinib plus MTX combination therapy.

### Secondary objectives

2.2

Following upadacitinib administration, disease activity will be assessed by MSUS. We will explore whether patients’ baseline parameters, including clinical disease activity indices, MSUS scores, and serum biomarkers, can predict a clinical response after the administration of upadacitinib. In addition, we will explore whether patients’ parameters, including clinical disease activity indices, MSUS scores, and serum biomarkers at the discontinuation of MTX, can predict a nonclinical relapse after the discontinuation of upadacitinib.

## Methods/design

3

### Study design

3.1

The study was designed in accordance with the Standard Protocol Items: Recommendations for Interventional Trials and Consolidated Standards of Reporting Trials 2010 guidelines^[7,8]^ (Additional File 1). The proposed study is a prospective, open-label, single-arm, and interventional clinical trial that will be conducted at the following 53 centers: Nagasaki University Hospital, Hokkaido University Hospital, Hokkaido Medical Center for Rheumatic Diseases, Katayama Orthopedic Rheumatology Clinic, University of Tsukuba Hospital, Saitama Medical University Hospital, Aoki Medical Clinic, Chiba University Hospital, Yokohama City University Medical Center, Yokohama City University Hospital, Yokohama Minami Kyousai Hospital, Yoshimi Hospital, Toyota Kosei Hospital, Chubu Rosai Hospital, Kyoto University Hospital, University Hospital Kyoto Prefectural University of Medicine, Osaka Medical and Pharmaceutical University Hospital, Osaka City University Hospital, National Hospital Organization Osaka Minami Medical Center, Kindai University Hospital, Kita-Harima Medical Center, Kobe University Hospital, Okayama University Hospital, Yamaguchi Prefectural Welfare Agricultural Cooperative Association Nagato General Hospital, Kagawa University Hospital, Ehime University Hospital, Kochi Medical School Hospital, Hospital of the University of Occupational and Environmental Health, Tobata General Hospital, PS Clinic, National Hospital Organization Ureshino Medical Center, National Hospital Organization Miyakonojo Medical Center, Miyazaki Zenjinkai Hospital, Chiyoda Hospital, Yoshitama Clinic for Rheumatic Diseases, Eiraku Clinic, Japanese Red Cross Nagasaki Genbaku Hospital, National Hospital Organization Nagasaki Medical Center, Sasebo Chuo Hospital, Sasebo City General Hospital, Fukushima Medical University Hospital, Toho University Ohashi Medical Center, Niigata Rheumatic Center, Nara Medical University Hospital, Tohoku Medical and Pharmaceutical University Wakabayashi Hospital, Aomori Prefectural Central Hospital, Nippon Medical School Hospital, Kurume University Medical Center, Seirei Hamamatsu General Hospital, Marunouchi Hospital, St. Marianna University Hospital, Japanese Red Cross Ogawa Hospital, and Shinonoi General Hospital.

In total, 155 RA patients will receive upadacitinib for a duration of 48 weeks. The study design is summarized in Figure 1.

**Figure 1 F1:**
[figure not shown]
Study design.

### Approvals

3.2

The study protocol was approved by the certified review board (CRB) of Nagasaki University (CRB approval no.: CRB20-024) and is registered with the Japan Registry of Clinical Trials (https://jrct.niph.go.jp) as jRCTs071200079 and ClinicalTrials.gov (https://clinicaltrials.gov/) as NCT05121298. The study will be conducted in accordance with the study protocol, the principles of the Declaration of Helsinki, the Clinical Trials Act (Act No. 16 of April 14, 2017), the Act on the Protection of Personal Information, and all other pertinent regulations. Participants will be provided with an explanation regarding the study by their treating rheumatologist and asked to voluntarily sign an informed consent form before participation.

### Participants

3.3

#### Inclusion criteria

3.3.1

Patients must meet all of the following requirements prior to consideration for study inclusion: (1) age ≥20 years; (2) diagnosis of RA based on the American College of Rheumatology/EULAR 2010 RA Classification Criteria^[10]^; (3) at least moderate disease activity defined as a Disease Activity Score 28 (DAS28)-C reactive protein (CRP) score of >3.2 at the time of eligibility evaluation; (4) at least one power Doppler (PD)-positive joint of 22 joints examined by MSUS at the time of eligibility evaluation, (5) treatment with MTX for ≥8 weeks prior to providing consent, including 4 weeks or more at the same dosage of 6–16 mg per week; and (6) ability and willingness to provide written informed consent and comply with the requirements of the study protocol.

#### Exclusion criteria

3.3.2

The exclusion criteria are as follows: (1) concurrent use of a corticosteroid equivalent to >7.5 mg/d of prednisolone; (2) applicable an item for the contraindication of upadacitinib (3) previous use of a JAK inhibitor; (4) treatment with a corticosteroid and change in dosage within 4 weeks prior to providing consent; (5) treatment with a csDMARD, other than MTX, within 2 weeks prior to providing consent; (6) treatment with a biologic DMARD or a biosimilar DMARD (i.e., infliximab, biosimilar of infliximab, adalimumab, golimumab, certolizumab pegol, tocilizumab, sarilumab, or abatacept) within 8 weeks prior to providing consent; (7) treatment with a tumor necrosis factor (TNF) inhibitor (i.e., etanercept or biosimilar of etanercept) within 4 weeks prior to providing consent; (8) use of a prohibited drug or therapy, other than the agents noted above, within 4 weeks prior to providing consent; (9) any complication, other than RA, causing a musculoskeletal disorder (i.e., ankylosing spondylarthritis, reactive arthritis, psoriatic arthritis, crystal-induced arthritis, systemic lupus erythematosus, systemic scleroderma, inflammatory myopathy, or mixed connective tissue disease); (10) current pregnancy, breastfeeding, or noncompliant with a medically approved contraceptive regimen during and 12 months after the study period; or (11) inappropriateness for inclusion in this study as determined by the investigators.

#### Intervention

3.3.3

Patients will receive upadacitinib at 15 mg/day and continue to receive the same dosage of MTX with or without a corticosteroid for 24 weeks (Stage I). If a EULAR-defined moderate response or a DAS28-CRP score of ≤3.2 is achieved at 12 weeks with a DAS28-CRP score of <2.6 at 24 weeks, MTX will be discontinued and upadacitinib with or without a corticosteroid will be continued until week 48 (Stage II). Patients not achieving a EULAR-defined moderate response and a DAS28-CRP score of ≤3.2 at 12 weeks or <2.6 at 24 weeks will be excluded from this study.

During the study period, the following treatments are prohibited: administration of a bDMARD or JAK inhibitor, other than upadacitinib; concomitant use of an immunosuppressant (i.e., azathioprine, cyclophosphamide, or cyclosporine), csDMARD, other than MTX, or an oral corticosteroid equivalent to >7.5 mg/day of prednisolone; intra-articular corticosteroid injections at the joints; and any nonsteroidal anti-inflammatory drug suppository. During the study period, the dosage of any oral nonsteroidal anti-inflammatory drug can be modified within the range approved in Japan.

#### Patient discontinuation criteria

3.3.4

A patient may be prematurely withdrawn from the study for the following reasons:

Discontinuation of upadacitinib for more than 7 consecutive daysFailure to achieve a EULAR-defined moderate response and a DAS28-CRP score of ≤3.2 at week 12Failure to achieve a DAS28-CRP score of <2.6 at week 24Discontinuation of MTX for more than 2 consecutive weeks during Stage IAny clinical relapse, defined as an increase in a DAS28- erythrocyte sedimentation rate (ESR) score of ≥3.2 due to elevated disease activity of RA, after discontinuation of MTXPatient request to quit the trialPatient request to change or discontinue treatmentAny AE inhibiting continued participationPregnancyDiscretion of the principal investigator to discontinue trial participation to ensure patient safety

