### Outcome measurements

3.4

Study visits will be conducted at baseline and 12, 24, 36, and 48 weeks after initiation of upadacitinib administration. The assessments are presented in Table 1. Clinical physicians will be blinded to joint assessments by MSUS.

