#### Clinical disease activity

3.4.1

Clinical disease activity will be evaluated by each attending physician (Japan College of Rheumatology-certified rheumatologists) based on the values of the DAS28-ESR, DAS28-CRP score, clinical disease activity index (CDAI), simplified disease activity index (SDAI), and the EULAR response criteria.^[11]^ At each visit, 28 joints, including the bilateral glenohumeral, elbow, wrist, metacarpophalangeal (MCP), interphalangeal, proximal interphalangeal of the hand, and knee joints, will be assessed for tenderness and swelling. Global and pain assessment and evaluator global assessment of each patient will be established on a 0–100-mm visual analog scale, and functional assessment will be scored according to the Health Assessment Questionnaire-Disability Index (HAQ-DI).

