#### Primary endpoint

3.5.1

The primary endpoint is maintenance of a DAS28-CRP score of ≤3.2 from week 24 to 48 in patients who achieve a DAS28-CRP score of <2.6 at week 24.

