#### Secondary endpoints

3.5.2

The secondary endpoints of this study are as follows: (1) achievement of a DAS28-CRP score of ≤3.2 at weeks 12, 24, and 36; (2) achievement of a DAS28-CRP score of <2.6 at weeks 12, 24, 36, and 48; (3) clinical relapse (DAS28-CRP score of >3.2) at week 48 in patients who achieved a DAS28-CRP score of <2.6 at week 24; (4) achievement of an EULAR-defined moderate response at week 12; (5) changes in DAS28-ESR and DAS28-CRP scores from baseline to weeks 12, 24, 36, and 48; (6) changes in DAS28-ESR and DAS28-CRP scores from week 24 to 36 and 48; (7) changes in CDAI and SDAI values from baseline to weeks 12, 24, 36, and 48; (8) changes in CDAI and SDAI values from week 24 to 36 and 48; (9) achievement of a CDAI of ≤2.8 at weeks 12, 24, 36, and 48; (10) achievement of a SDAI of ≤3.3 at weeks 12, 24, 36, and 48; (11) changes in biomarker serum levels from baseline to weeks 12, 24, 36, and 48; (12) changes in biomarker serum levels from week 24 to 36 and 48; (13) changes in total PD and GS scores and combined PD score from baseline to weeks 12, 24, 36, and 48; (14) changes in total PD and GS scores and combined PD score from week 24 to 36 and 48; (15) change in vdH-mTSS from baseline to weeks 24 and 48; (16) change in vdH-mTSS from week 24 to 48; (17) change in the HAQ-DI data from baseline to weeks 12, 24, 36, and 48; and (18) change in the HAQ-DI data from week 24 to 36 and 48.

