### Statistical analysis

3.9

The primary analysis is planned to estimate the 95% CI of the primary endpoint (section 3.5.1) via Wilson's score interval.^[12]^ The primary endpoint will be evaluated from a set of participants who achieved a DAS28-CRP score of <2.6 during upadacitinib plus MTX combination therapy (Stage I). The primary analysis will control for type I errors at the 5% significance level. To support the clinical interpretation of the results of the primary analysis, participant-wise time courses of the DAS28-ESR and DAS28-CRP scores will be plotted. The distribution of changes in the total PD and GS scores and the combined PD scores will be summarized as histograms. Other statistical analyses are planned to explore the relationships between the measured results obtained as exploratory outcomes, as detailed in section 3.5.3. All other analyses will be considered as exploratory and will not be adjusted for multiplicity.

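### Stage II relapse withdrawal is set on DAS28-ESR ≥3.2 but the primary endpoint on DAS28-CRP ≤3.2, so a patient still meeting the endpoint can be withdrawn as relapsed before week 48

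*Protocol article*

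**What the plan says.** Section 3.3.4 introduces its list with "A patient may be prematurely withdrawn from the study for the following reasons". One of the reasons, applying after MTX has been stopped, is "clinical relapse, defined as an increase in a DAS28- erythrocyte sedimentation rate (ESR) score of ≥3.2 due to elevated disease activity of RA".

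The endpoints use the other score. Section 3.5.1 states: "The primary endpoint is maintenance of a DAS28-CRP score of ≤3.2 from week 24 to 48". Secondary endpoint 3 in section 3.5.2 is "clinical relapse (DAS28-CRP score of >3.2) at week 48".

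Three other statements bear on the consequence:

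- Section 3.9, on the analysis set: "The primary endpoint will be evaluated from a set of participants who achieved a DAS28-CRP score of <2.6", reached during Stage I.
- Section 3.4, on timing: "Study visits will be conducted at baseline and 12, 24, 36, and 48 weeks after initiation of upadacitinib administration". Week 36 is thus the only scheduled visit strictly between weeks 24 and 48.
- Section 3.4.1: disease activity is assessed "based on the values of the DAS28-ESR, DAS28-CRP score" and other indices, so both scores are collected and treated as separate measures.

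**The concern.** The same term, clinical relapse, carries two operational definitions. The one that can end a patient's follow-up is not the one that decides the primary endpoint. Every other criterion in sections 3.3.3 and 3.3.4 with a numerical DAS28 threshold (weeks 12 and 24) uses DAS28-CRP. So do eligibility in 3.3.1 and the analysis set in 3.9.

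If a patient is withdrawn at week 36 on the ESR score alone, that patient stays in the primary set, but follow-up may stop before the week-48 DAS28-CRP that the endpoint needs. The primary proportion would then depend partly on a relapse rule that is not the endpoint. The trial has a single arm and this proportion is its principal objective, so no comparison group offsets such a bias.

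**Working it through.** **Definitions side by side**

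| Use | Score | Relapsed | Not relapsed | Exactly 3.2 |
|---|---|---|---|---|
| Withdrawal in Stage II (3.3.4) | DAS28-ESR | ≥3.2 | <3.2 | relapsed |
| Primary endpoint (3.5.1) | DAS28-CRP | >3.2 | ≤3.2 | maintained |
| Secondary endpoint 3 (3.5.2) | DAS28-CRP | >3.2 | ≤3.2 | not relapsed |

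The wording in 3.3.4 is loose. It is read here as a rise *to* 3.2 or more, which is its natural sense.

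**The four combinations at week 36**

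- CRP ≤3.2, ESR <3.2: maintained, follow-up continues. No conflict.
- CRP >3.2, ESR ≥3.2: endpoint failed, withdrawal allowed. No conflict.
- CRP >3.2, ESR <3.2: endpoint failed, relapse withdrawal not triggered. The failure has already been observed, so the primary estimate is unharmed.
- CRP ≤3.2, ESR ≥3.2 attributed to RA: endpoint still met, withdrawal allowed. This is the problem case.

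Entry to Stage II (3.3.3) sets no DAS28-ESR limit, so nothing ensures that entrants start well below the ESR threshold. At week 48 both scores are recorded, so the problem case can cost data only before then.

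**The plan's own figures**

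Inputs from section 3.8: expected proportion p = 0.65, half-width 0.10, 60% reaching Stage II, 10% dropout. From section 3.9: Wilson interval. With z = 1.96, the half-width is

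w = z·√[p(1−p)/n + z²/(4n²)] / (1 + z²/n)

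- n = 83: w = 0.1005
- n = 84: w = 0.09996, the first n with w ≤ 0.10. The stated 84 is reproduced.
- 84/0.60 = 140, as stated.
- 140/0.90 = 155.6, against the stated 155.

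**Illustration of what is at stake**

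With 84 Stage II patients and p = 0.65, 0.65 × 84 = 54.6, taken as 55 maintainers: 55/84 = 0.655, Wilson 95% interval 0.548–0.748.

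Suppose k of these 55 are withdrawn before week 48 on the ESR rule alone, and would otherwise have stayed maintained to week 48. The range of k is an assumption (about 5%, 10% and 20% of 55). Counted as failures, the estimate is (55−k)/84. Excluded, it is (55−k)/(84−k).

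| k | As failures (95% interval) | Shift | Excluded (95% interval) | Shift |
|---|---|---|---|---|
| 3 | 52/84 = 0.619 (0.512–0.716) | 0.036 | 52/81 = 0.642 (0.533–0.738) | 0.013 |
| 6 | 49/84 = 0.583 (0.477–0.683) | 0.071 | 49/78 = 0.628 (0.517–0.727) | 0.027 |
| 11 | 44/84 = 0.524 (0.418–0.627) | 0.131 | 44/73 = 0.603 (0.488–0.707) | 0.052 |

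Where the shift first exceeds 0.10:

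- As failures: 8/84 = 0.095, 9/84 = 0.107, so k = 9 (9/55 = 16%).
- Excluded: k = 18 gives 37/66 = 0.561, shift 0.094; k = 19 gives 36/65 = 0.554, shift 0.101. So k = 19 (19/55 = 35%).

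If such patients were instead kept as maintained on their week-36 value, the illustration would not move: 55/84 either way.

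**The case against.** A withdrawal rule for patient care need not match the endpoint, and the route to harm is narrow. The ESR score must reach 3.2 while the CRP score does not exceed it, the rise must be attributed to RA, the investigator must use a permissive rule, and this must happen before week 48. How a withdrawn patient is counted is ordinarily settled in the analysis plan, which is not shown. Table 1 is also not shown, so later or discontinuation-visit assessments cannot be ruled out. The 5–20% range has no source in the documents. The ESR wording may simply be a slip for CRP. And an amendment to an approved protocol run at 53 centers is more than an edit on paper.

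Most of this limits the size and stands as such. The loss of week-48 values is plausible rather than shown, and for much of the assumed range the shift is smaller than the planned precision. It does not remove the conflict. The point is two stated definitions that disagree, not a missing detail. An analysis plan can classify a withdrawn patient, but it cannot recover a score that was not collected. The permissive wording also leaves discordant cases to judgement at 53 open-label sites, so handling can vary. If ESR is a slip, sites still act on what is written.

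**Conclusion.** The concern holds. As written, section 3.3.4 permits withdrawal for relapse of a patient who still meets the primary endpoint and who remains in the primary analysis set. The mismatch covers both the marker and the boundary value, and it is certain from the text.

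Its effect on the estimate is not known, because the documents give no rate of ESR/CRP disagreement. Under the assumed 3 to 11 losses among 55 maintainers, the estimate falls by 0.036 to 0.131 if losses count as failures and by 0.013 to 0.052 if they are excluded. This rests on two further assumptions: that no DAS28-CRP is obtained after withdrawal, and that these patients would have stayed at or below 3.2. Taking them out of the numerator in either way lowers the estimate. The point should be corrected, but it does not by itself undermine the design.

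**What to change.** Reword the criterion in 3.3.4 as an increase to a DAS28-CRP score of >3.2 due to elevated RA disease activity, matching 3.5.1 and 3.5.2(3). A patient withdrawn for relapse has then already failed the primary endpoint, so the withdrawal no longer costs the primary analysis any information.

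If the ESR rule is wanted for clinical reasons, state that it is separate from endpoint relapse and keep collecting DAS28-CRP to week 48 at the scheduled visits. Fix one primary classification for ESR-only withdrawals (for example, not maintained), report their number, and give one sensitivity analysis with the other classification. The first option is preferable, because scores taken after withdrawal may reflect changed treatment.

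Cost: one line of protocol wording, issued as an amendment to the participating centers. Both scores are already collected, no scheduled visit is added, and 84, 140 and 155 stand. The fallback adds one sensitivity analysis.
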